### Strategies to improve adherence to interventions {11c}

Participants are able to contact a study nurse via mail or phone call at any time for questions or technical support with the PNS system. Additionally, study investigators are contacting the participants at each follow-up visit and examine wound healing and stimulation settings together with the technicians from Boston Scientific.

### Relevant concomitant care permitted or prohibited during the trial {11d}

Concomitant intervention for sacroiliac joint pain is prohibited during the trial. This applies for both study groups. After randomization, it will not be allowed to receive other treatment modalities such as intraarticular injections, radiofrequency ablation, cryoablation or sacroiliac joint fusion.

### Provisions for post-trial care {30}

Participants with PNS are regularly seen at neuromodulation outpatient clinic in post-trial care.

There is no anticipated harm and compensation for trial participation. No provision for post-trial care will not be conducted.

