**Fig. 2 Fig2:**
[figure not shown]
Postoperative sagittal X-rays of two different patients with placement of the leads close to the sacral surface. **A** Patient with unilateral lead. **B** Patient with bilateral leads

The part of the extension lead protruding the skin is sutured sturdily and connected to the external stimulator. After successful trial phase of 3–14 days patients with at least 50% pain reduction in NRS score, patients receive the implantation of the impulse generator (WaveWriter Alpha™, Boston Scientific, MA, USA), which will be connected to the stimulation lead for permanent stimulation. The extension will be discarded. Therefore, the extension lead is cut close to the skin and removed. The impulse generator is then inserted subcutaneously into the initially prepared subcutaneous pocket. Therefore, the skin incision is widened to a 5–6-cm skin incision, the impulse generator is fixed with a suture and the generator is connected to the lead.

If patients did not experience a 50% pain relief, the leads will be explanted.

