### Outcomes {12}

The primary outcome is the difference in Numeric Pain Rating Scale (NRS) between baseline and after 6 months.

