#### Secondary outcomes

Proportion of patients with ≥ 50% reduction in sacroiliac joint pain (responder) on the NRS (0–100) at 6 and 12 months.Improvement of pain associated disability (ODI) after 6 and 12 months.Improvement of Health-related quality of life after 6 and 12 months.Difference in Numeric Pain Rating Scale (NRS) between baseline and after 12 months.

Clinical relevance and standardization of NRS and ODI has been validated previously. The majority of clinical trials on PNS are monitoring outcomes by NRS and ODI (15–18).

Health economics outcomes:Ability to work, if patients were unable to work because of the chronic back painDoctor visits after inclusion in the study

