## Participant timeline {13}

Participants will participate in the study for 12 months.All patients in the BMT group receive best medical treatment for chronic back pain in the outpatient department and receive physiotherapy treatment for at least 2 months.Patients in the PNS group receive the following procedure:Patients will be prepared for the surgical procedure with blood sample, informed consent and potentially further diagnostic procedures.The surgery will be performed with analgesic sedation or in general anaesthesia:

Percutaneous implantation of the lead (unilateral/bilateral). Connection to extension and externalization

Trial phase for 3–14 days with NRS monitoring.

After trial phase, only patients with at least 50% reduction of pain (NRS) receive the impulse generator gluteal/abdominal for permanent stimulation.

The study schedule is presented in Table 1.

**Table 1 Tab1:** Study schedule

	Screening	V1 (day 1)	V2 (after trial)	V3 (3 months ± 30 days)	V4 (6 months ± 30 days)	V5 (12 months ± 60 days)	Time expenditure (min.)
NRS (0–10) (1 item)	x	x	x	x	x	x	6 × 10 60
ODI (10 items)		x		x	x	x	4 × 20 80
SF-36 (36 items)		x		x	x	x	4 × 30 120
ADS-K		x		x	x	x	4 × 30 120
Patient satisfaction with pain relief (0–10) (1 item)		x		x	x	x	4 × 10 40
PSQI (24 items)		x		x	x	x	4 × 20 80
Neurological status (50 items)		x	x	x	x	x	5 × 30 150
IPG-data (15 items)			x	x	x	x	4 × 30 120

*NRS* Numeric Pain Rating Scale, *ODI* Oswestry Disability Index, *SF-36* The Short Form (36) Health Survey, *ADS-K* General Depression Scale, *PSQI* Pittsburgh Sleep Quality Index, *IPG* implantable pulse generators

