## Sample size {14}

Based on our own preliminary data of 10 patients, a mean decrease in NRS score of 3.5 points (standard deviation = 3.1) was observed in the PNS group, whereas the reduction in the BMT group was 1.4 points (standard deviation = 1.7). Childs et al. have previously reported a 2-point difference on the NRS to be clinically meaningful in a multicenter, randomized trial [13].

To detect the observed difference (2.1 points in reduction in NRS score) with an estimated standard deviation of 3, a two-sided error of 5% with a power of 80% using an unpaired *t*-test, a case number of 34 per group is needed. Thus, taking into account the 25% non-responders in the PNS group, one would need 46 patients in the intervention group and use a randomization of 4:3 accordingly. Adding 10% additional dropouts, one would need to include a total of 90 patients (52 in the PNS group and 38 in the BMT group) in the study. The sample size planning was performed using nQuery version 7.0. The planning in this study was performed by the study sponsor in collaboration with the local Institute of Biometry and Clinical Epidemiology.

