### Adverse event reporting and harms {22}

After participants have provided consent and been enrolled in the study, adverse events will be documented and recorded until the end of the study period. Any serious adverse event that occurs due to intervention or evaluation will be reported to the institutional review board and the research team of this study will take responsibility for the treatment.

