### Frequency and plans for auditing trial conduct {23}

An annual audit will be conducted to protect the integrity of all collected data and study procedures as part of this trial. The principal investigator will ensure that data management is conducted and reported according to the protocol. The Project Management Group will meet weekly to review trial conduct through the study period. Annual auditing trials are planned to ensure the study protocol is followed.

A Data Monitoring Committee was not considered for this study as the intervention of this trial is considered as low risk.

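### Patient-requested removal of the PNS system is tied to withdrawal, which stops data collection, so its complications can go uncounted; the outcome list also names no harm measure

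*Protocol article*

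**What the plan says.** **When recording stops.** Adverse event reporting and harms {22} states that, once patients have consented and enrolled, "adverse events will be documented and recorded until the end of the study period". It makes no distinction by arm. Serious events caused by the intervention or by study assessments go to the institutional review board. Criteria for discontinuing or modifying allocated interventions {11b} lets PNS patients have the system taken out at any time if they wish to leave the study. It then says that the team gathers nothing more from patients who have left and keeps what it already holds. Plans to promote participant retention {18b} arranges one closing outpatient visit for patients who want to leave.

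**Procedures.** Participant timeline {13} gives the first step in the PNS arm: "Percutaneous implantation of the lead (unilateral/bilateral). Connection to extension and externalization". Intervention description {11a} then has either generator implantation through a widened incision or, for the others, "If patients did not experience a 50% pain relief, the leads will be explanted". Sample size {14} is inflated by "taking into account the 25% non-responders in the PNS group".

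**Outcomes.** Under Outcomes {12}, "The primary outcome is the difference in Numeric Pain Rating Scale (NRS) between baseline and after 6 months". The secondary outcomes are the 50% responder proportion, disability ("Improvement of pain associated disability (ODI) after 6 and 12 months"), quality of life and the 12-month pain change. Two health-economics items follow. None of these is a harm measure.

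**Statements on risk.** Provisions for post-trial care {30}: "There is no anticipated harm and compensation for trial participation". The auditing section {23}: "A Data Monitoring Committee was not considered for this study as the intervention of this trial is considered as low risk".

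**The concern.** The trial compares an implanted device with non-surgical care, so a reader will weigh pain relief against complications, reoperations and removals. That weighing needs harm counts that are complete and comparable between arms.

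Two features of the plan work against this. First, the data-collection rule in {11b} and the recording rule in {22} give different end points for the same patient. If a site follows {11b}, collection can stop at about the time a removal operation takes place. The withdrawal rule covers both arms, but a BMT patient has no device to remove before the month-6 switch option in Trial design {8}. The loss therefore runs in one direction and makes PNS look safer.

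Second, the section that fixes what the trial will report lists benefit and health-economics measures only. The one general sentence on expected harm says there is none.

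**Working it through.** **1. The plan's own figures.** Inputs from Sample size {14}: difference 2.1, SD 3, two-sided 5%, power 80%, unpaired t-test, 25% non-responders in the PNS arm, 10% dropout.
- Standardised difference 2.1 / 3 = 0.70. The exact t-test calculation gives 33.02 per group, rounded up to 34, as stated.
- PNS arm: 34 / 0.75 = 45.3, so 46.
- Dropout: 46 / 0.9 = 51.1, so 52; 34 / 0.9 = 37.8, so 38. Total 52 + 38 = 90, as stated.

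The sample size reproduces, and nothing below alters it.

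**2. Procedures in the PNS arm.** A patient who completes the trial phase has lead implantation, then generator implantation or lead explantation: two procedures.
- If all 52 complete it: 2 × 52 = 104 procedures. If only the 46 before dropout inflation do: 2 × 46 = 92.
- The BMT arm has no trial operation before month 6.

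**3. Expected explantations after the trial phase.** 0.25 × 52 = 13, or 0.25 × 46 = 11.5 on the smaller base. This takes the 25% to be trial-phase failures. That is the natural reading, but {14} does not say so, and the secondary outcomes also use the term responder for months 6 and 12.

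**4. When recording stops, section by section.**
- {22}: adverse events are recorded through to study end, for all enrolled patients.
- {11b}: nothing more is collected after a patient leaves. The only route it describes to removal at the patient's request is through leaving the study.
- {18b}: one closing visit, with no statement that it falls after the removal operation.
- {11a}: explantation after a failed trial phase, which no section calls withdrawal.

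Trial-phase failures therefore stay under {22}, and their events should be recorded. The exposed group is patients who leave the study and have the system removed. If the closing visit comes before removal, wound or other complications of that operation fall outside data collection under {11b} but inside it under {22}.

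**5. How many patients this could touch.** The documents give no rate of removal on request. As an assumption, take the plan's own dropout allowance in the PNS arm, 52 − 46 = 6. If none of these patients leaves with removal the gap is 0; if all do, it is 6.

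**6. The no-harm sentence against the rest of the plan.** {11a} describes surgery under sedation or general anaesthesia, with an extension passing through the skin for 3–14 days. Strategies to improve adherence {11c} plans wound checks at follow-up visits. {22} provides for serious events caused by the intervention. {23} calls the risk low, which is not the same as none. The {30} sentence fits none of these.

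**The case against.** The strongest reply is that harms are collected. {22} covers both arms from enrolment. Wound checks and a neurological examination are scheduled, and disability and quality-of-life scores would worsen if complications troubled patients. How adverse events are tabulated by arm is commonly left to the full protocol or analysis plan, and neither is shown. The {30} sentence concerns post-trial care and compensation and enters no hypothesis or analysis. The closing visit in {18b} narrows the gap after withdrawal. All of this stands, and it limits the point.

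It does not settle two things. The documents give conflicting end points for recording, and {18b} does not place its visit after removal. Choosing the trial's outcomes is the task of {12}, which names no harm outcome.

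Some stronger readings are tempting, but the documents do not support them:
- *PNS would be judged on benefit alone.* This is true of the listed outcomes only. Adverse events are recorded, and their presentation may be set out elsewhere.
- *Every PNS patient has at least two operations.* The 52 include a dropout allowance, so some may have one or none.
- *A quarter have leads removed without benefit.* The rule is relief below 50%, which may be partial, and the 25% is a planning assumption.
- *Harms in the 13 expected trial-phase failures would be lost.* Nothing treats those patients as withdrawn.
- *The low-risk label is wrong.* The documents give no complication rate by which to judge it.
- *The trial is too small to show absence of harm.* With 0 events in 52 the one-sided 95% upper limit is 1 − 0.05^(1/52) = 5.6%. That holds for any arm of 52, and the plan never claims to show absence of harm.

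**Conclusion.** The point holds in a limited form. {11b} and {22} conflict over whether adverse events are recorded after a patient leaves with the device removed. Followed literally, {11b} can leave complications of removal uncounted, and before month 6 only in the PNS arm. The number exposed cannot be read from the documents; on the dropout allowance it lies between 0 and 6 of 52. That is few patients, but serious complications may also be few, and the error has a known direction.

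Alongside this, {12} names no harm measure for a comparison in which about 13 of 52 PNS patients are expected to have leads explanted, if the 25% means trial-phase failure. The no-harm wording in {30} is contradicted elsewhere in the article. It is a wording fault that drives no analysis. No estimate, power figure or primary result is affected.

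**What to change.** 1. Reconcile {11b}, {18b} and {22}. State that explantation alone does not count as leaving the study, and that adverse-event recording continues after explantation or withdrawal through to study end, subject to the patient's consent. Say where the closing visit falls relative to any removal operation.
2. Add a named safety outcome to {12}, built from events already recorded: procedure- or device-related complications, reoperation or explantation, and serious adverse events. Report each by randomised arm to month 6, before BMT patients can switch, with 95% CIs. The plan already treats all its p-values as exploratory, so this raises no multiplicity question.
3. Correct the sentence in {30} so that it agrees with {11a}, {11c}, {22} and {23}.

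The cost is a protocol wording change, one extra table and modest follow-up of patients who withdraw, which may need matching consent wording. Sample size, power and the primary analysis stay as they are.

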### Outcomes {12}

The primary outcome is the difference in Numeric Pain Rating Scale (NRS) between baseline and after 6 months.

#### Secondary outcomes

Proportion of patients with ≥ 50% reduction in sacroiliac joint pain (responder) on the NRS (0–100) at 6 and 12 months.Improvement of pain associated disability (ODI) after 6 and 12 months.Improvement of Health-related quality of life after 6 and 12 months.Difference in Numeric Pain Rating Scale (NRS) between baseline and after 12 months.

Clinical relevance and standardization of NRS and ODI has been validated previously. The majority of clinical trials on PNS are monitoring outcomes by NRS and ODI (15–18).

Health economics outcomes:Ability to work, if patients were unable to work because of the chronic back painDoctor visits after inclusion in the study

## Participant timeline {13}

Participants will participate in the study for 12 months.All patients in the BMT group receive best medical treatment for chronic back pain in the outpatient department and receive physiotherapy treatment for at least 2 months.Patients in the PNS group receive the following procedure:Patients will be prepared for the surgical procedure with blood sample, informed consent and potentially further diagnostic procedures.The surgery will be performed with analgesic sedation or in general anaesthesia:

Percutaneous implantation of the lead (unilateral/bilateral). Connection to extension and externalization

Trial phase for 3–14 days with NRS monitoring.

After trial phase, only patients with at least 50% reduction of pain (NRS) receive the impulse generator gluteal/abdominal for permanent stimulation.

The study schedule is presented in Table 1.

**Table 1 Tab1:** Study schedule

	Screening	V1 (day 1)	V2 (after trial)	V3 (3 months ± 30 days)	V4 (6 months ± 30 days)	V5 (12 months ± 60 days)	Time expenditure (min.)
NRS (0–10) (1 item)	x	x	x	x	x	x	6 × 10 60
ODI (10 items)		x		x	x	x	4 × 20 80
SF-36 (36 items)		x		x	x	x	4 × 30 120
ADS-K		x		x	x	x	4 × 30 120
Patient satisfaction with pain relief (0–10) (1 item)		x		x	x	x	4 × 10 40
PSQI (24 items)		x		x	x	x	4 × 20 80
Neurological status (50 items)		x	x	x	x	x	5 × 30 150
IPG-data (15 items)			x	x	x	x	4 × 30 120

*NRS* Numeric Pain Rating Scale, *ODI* Oswestry Disability Index, *SF-36* The Short Form (36) Health Survey, *ADS-K* General Depression Scale, *PSQI* Pittsburgh Sleep Quality Index, *IPG* implantable pulse generators

## Sample size {14}

Based on our own preliminary data of 10 patients, a mean decrease in NRS score of 3.5 points (standard deviation = 3.1) was observed in the PNS group, whereas the reduction in the BMT group was 1.4 points (standard deviation = 1.7). Childs et al. have previously reported a 2-point difference on the NRS to be clinically meaningful in a multicenter, randomized trial [13].

To detect the observed difference (2.1 points in reduction in NRS score) with an estimated standard deviation of 3, a two-sided error of 5% with a power of 80% using an unpaired *t*-test, a case number of 34 per group is needed. Thus, taking into account the 25% non-responders in the PNS group, one would need 46 patients in the intervention group and use a randomization of 4:3 accordingly. Adding 10% additional dropouts, one would need to include a total of 90 patients (52 in the PNS group and 38 in the BMT group) in the study. The sample size planning was performed using nQuery version 7.0. The planning in this study was performed by the study sponsor in collaboration with the local Institute of Biometry and Clinical Epidemiology.

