## Statistical methods

### Statistical methods for primary and secondary outcomes {20a}

The primary endpoint will be analysed by mixed linear regression with the change in NRS score from baseline to 6 [12] months as dependent and treatment and baseline value as independent variables. Study center will be added as a random intercept. In order to adjust for relevant covariables, a maximum of four additional variables are included in the model due to the sample size limitations. By this procedure, depending on the correlation of the independent variables with the dependent variable, a gain in power is obtained compared with the calculated sample size [14]. Even in the worst case and a correlation of 0, however, at least the power as specified in the sample size calculation is achieved. As a further analysis to investigate time trends, we will apply a linear mixed effects models as before but consider all time points and include timepoint as an additional, discrete factor. Further, the interaction between treatment and timepoint and a random intercept for the patients will be added.

A chi-square test is used to analyse the proportion of patients with at least a 50% reduction in the NRS value. In a second step, if there are enough patients with a corresponding reduction, a mixed logistic regression model with additional covariates and study center as random intercept is created. The secondary endpoints will be analysed analogously to the primary endpoint. All analyses including *p*-values are to be considered purely exploratory. All results will be reported with 95% CIs.

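### The stated 80% power belongs to about 34 PNS trial-phase responders versus 34 BMT patients, not to the comparison as randomised, because the 25% non-responders are counted as lost cases.

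*Protocol article*

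**What the plan says.** Sample size {14} takes its inputs from a pilot of 10 patients: "a mean decrease in NRS score of 3.5 points (standard deviation = 3.1) was observed in the PNS group", while "the reduction in the BMT group was 1.4 points (standard deviation = 1.7" points is given as its SD. The target is set as follows: "To detect the observed difference (2.1 points in reduction in NRS score) with an estimated standard deviation of 3", with "a two-sided error of 5% with a power of 80% using an unpaired" t-test. This leads to 34 patients per group. The next step applies to one arm only: "Thus, taking into account the 25% non-responders in the PNS group, one would need 46 patients in the intervention group". The 4:3 allocation is derived from that step. A further 10% for additional dropouts gives 52 + 38 = 90.

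Trial design {8} places randomisation directly after consent. The 3–14 day lead trial takes place afterwards and only in the PNS arm. Intervention description {11a} says of those who fail it: "If patients did not experience a 50% pain relief, the leads will be explanted". It does not say that they leave the study. Participant timeline {13} has participants in the study for 12 months.

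Statistical methods {20a} models the change in NRS on treatment and baseline, with study center as a random intercept and up to four more covariates. It adds: "Even in the worst case and a correlation of 0, however, at least the power as specified in the sample size calculation is achieved".

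**The concern.** Dividing a sample size by (1 − p) replaces patients who supply no outcome. A PNS patient whose leads are removed after a failed trial phase can still give an NRS score at 6 months and still belongs to the PNS arm. Such a patient is a treatment failure, not a missing observation. Kept in the arm, these patients may lower its mean change, and a larger n at an undiluted 2.1-point difference does not allow for that.

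The calculation therefore fits only an analysis of PNS trial responders against all BMT patients. That would select one arm on an early post-randomisation pain response, with no matching selection in the other. If everyone is analysed as allocated, the printed 80% is not the power of the test. The same denominator question arises for the secondary endpoint of at least 50% NRS reduction. The step also fixed the total of 90 and the 4:3 ratio.

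**Working it through.** **1. Reproducing the plan's figures.** Inputs from Sample size {14}: difference 3.5 − 1.4 = 2.1, SD 3, two-sided 5%, two-sample t-test (noncentral t).
- 33 per group gives 79.97% power and 34 per group gives 81.2%, so 34 is needed.
- 34/0.75 = 45.3, rounded up to 46. 46/0.9 = 51.1, rounded up to 52. 34/0.9 = 37.8, rounded up to 38. Total 52 + 38 = 90.
- 46/34 = 1.35, close to 4:3.

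The arithmetic is correct.

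**2. What the 80% refers to.** 46 × 0.75 = 34.5 PNS trial responders. Power for 34.5 versus 34 at 2.1 points and SD 3 is 81%.

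**3. All randomised patients, 46 versus 34 evaluable.** Suppose 3.5 is the mean change in implanted patients, and let m be the mean change in non-responders. Then:
- Difference = 0.75 × 3.5 + 0.25 × m − 1.4.
- Mixture SD in the PNS arm = √(s² + 0.75 × 0.25 × (3.5 − m)²), where s is the within-group SD.
- Standard error = √(SD²/46 + SD²/34), each arm with its own SD. Power is from the noncentral t with 78 degrees of freedom.

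The protocol does not give m, so the values below are assumptions. For m = 1.4: 2.625 + 0.35 − 1.4 = 1.575. With SD 3 the standard error is 3 × √(1/46 + 1/34) = 0.678, the noncentrality is 1.575/0.678 = 2.32, and power is 63%. The other rows follow in the same way.

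| Assumption | Difference | Power, SD 3 in both arms | Power, mixture SD in PNS arm (s = 3) | Power, pilot SDs (3.1 with mixture; 1.7) |
|---|---|---|---|---|
| Non-responders change like BMT (m = 1.4) | 1.575 | 63% | 61% (SD 3.13) | about 80% |
| Non-responders do not change (m = 0) | 1.225 | 43% | 40% (SD 3.36) | about 54% |
| 3.5 already includes non-responders | 2.1 | 86% | not applicable | about 97% |

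In the last row the 25% inflation is not needed: about 70 evaluable patients at 4:3 (40 + 30) would give 80% power at SD 3. An intermediate case, in which non-responders keep half the benefit over BMT (m = 2.45), gives a difference of 1.84 and 76% power at SD 3.

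**4. If non-responders were excluded (illustration only).** Suppose PNS had no effect on the 6-month score, changes were normal with SD 3, and the lowest 25% on the trial-phase response were removed. The mean of the remaining PNS patients would rise by r × 3 × φ(z₀.₂₅)/0.75 = r × 3 × 0.318/0.75 = 1.27 × r, where r is the correlation between trial-phase and 6-month change. The article does not give r. For r = 0.3, 0.5 and 0.7 the bias is about 0.4, 0.6 and 0.9 NRS points in favour of PNS.

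**The case against.** **Exclusion is not stated.** A reader might infer from the division by 0.75, and from the word for additional dropouts, that non-responders will be left out of the primary analysis. The documents do not support that as a fact. Explantation is described without withdrawal, participation is set at 12 months, the model contains treatment without restriction to responders, and the missing-data section says that a missed visit does not make a dropout. Analysis sets may also be left to a statistical analysis plan that is not shown. This stands: the bias is conditional, and its size rests on correlations found nowhere in the article.

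**A loss of power is not established.** A reader might also infer that the trial is underpowered. That depends on whether 3.5 includes non-responders and on how explanted patients change by 6 months; neither is given. The planning SD of 3 is larger than the equal-weight pooled pilot SD of √((3.1² + 1.7²)/2) = 2.5, and baseline adjustment may add power. With the pilot SDs, the case in which non-responders change like BMT comes back to about 80%. This stands too, although SDs from 10 patients are imprecise and the plan itself chose 3. Such margins may offset dilution by chance; they do not make division by 0.75 a correction for it.

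**The power assurance in {20a} concerns covariates.** It says that adjustment should not cost power relative to the t-test. It is not a separate claim about non-responders; it only inherits the premise of the sample size section.

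**All analyses are called exploratory.** True, but the article still states a superiority hypothesis, a primary endpoint and 80% power, and a selected comparison would distort estimates and confidence intervals under any label.

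**Conclusion.** The concern holds in this form: the non-responder step is a missing-data correction applied to patients who can have outcome data, so the stated 80% does not describe the comparison that randomisation supports. At the planning SD of 3, with 46 versus 34 evaluable, power is about 61–63% or 40–43% under the two dilution assumptions, and 86% if the pilot mean already includes non-responders. With the pilot SDs it is about 80%, 54% and 97%. Which figure applies cannot be settled from the article. The flaw in the inflation step is certain; the direction and size of the power error are not. Any bias towards PNS arises only if non-responders are in fact excluded, which the article implies through its arithmetic but does not state.

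**What to change.** Keep N at 90 and change the wording:
- State that all randomised patients, including explanted trial-phase non-responders, are followed to 6 months and analysed in their assigned arm, for both the mean NRS change and the responder proportion.
- State whether the pilot mean of 3.5 includes trial-phase non-responders.
- Restate the power for that comparison, with the assumed change in non-responders and the SD used.
- Limit the power sentence in {20a} to the effect of covariate adjustment on the corrected figure.
- Report implanted PNS patients versus BMT only as a supportive, non-randomised comparison.

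The cost is protocol wording and a stated power that may be less favourable. No patients or visits are added.
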